# The feasibility of a crossover, randomized controlled trial design to assess the effect of probiotics and prebiotics on health of elite Swiss para-athletes: a study protocol

**DOI:** 10.1186/s40814-022-01048-6

**Published:** 2022-04-27

**Keywords:** Spinal cord injury, Probiotic, Prebiotic, Feasibility trial, Clinical trial design

## Abstract

**Background:**

Spinal cord injury (SCI) may cause an autonomic imbalance in the gastrointestinal tract, leading to deficits in colonic motility, mucosal secretions, vascular tone, and an increase of intestinal barrier permeability. Autonomic denervation and factors such as age, physical activity, antibiotic use and stress may cause intestinal bacterial translocation, decreased microbiota diversity, known as gut dysbiosis and thus increase susceptibility to experiencing gastrointestinal discomfort. Probiotic treatment in individuals with SCI may normalize the gut microbiota and improve overall health. We aim to assess the feasibility of probiotic and prebiotic intervention in athletes with SCI and collect information necessary for sample size calculation of a definite trial on improving health outcomes in para-athletes.

**Methods and analysis:**

Elite Swiss para-athletes (aged> 18 years), being shortlisted for the Paralympic Games 2021 in Tokyo or a member of a national team (*n* = 43), will be invited to participate in this single-center randomized crossover trial. Athletes suffering from chronic inflammatory bowel diseases, those currently taking antibiotics or other medication to alleviate gastro-intestinal complaints will not be eligible to be included in the study. Athletes will be randomized (1:1) to receive for 4 weeks a daily dose of either 3 g of probiotic preparation or 5 g of prebiotic (organic oat bran) supplementation in addition to usual diet, followed by a 4-week washout period or vice versa. The primary outcome is the feasibility of the study, measured by recruitment and dropout rates, feasibility of the measurements, acceptability and adherence to the intervention. Secondary outcomes include gastrointestinal health assessment, diet and training information, handgrip strength, blood diagnostic parameters, and intestinal microbiome characterization. The changes in clinically relevant secondary outcome values will be used to make a power calculation for definite trial.

**Discussion:**

This pilot trial will address two common challenges in SCI research: the difficulty to recruit enough participants for a sufficiently powered study and the ability to collect data within the limits of a realistic budget and time frame. Upon demonstrated feasibility of the intervention and study procedures, the intervention will be evaluated in a definitive controlled trial comprising a larger sample of para-athletes (elite, engaged, or recreationally active) individuals with a SCI.

**Trial registration:**

NCT04659408

## Introduction

Spinal cord injury (SCI) disrupts the autonomic nervous system, impairs its ability to coordinate organ function and leads to SCI–immune depression syndrome and autonomic dysreflexia [1]. The autonomic imbalance in the gastrointestinal (GI) tract can affect colonic motility, mucosal secretions and intestinal barrier permeability [2, 3]. Besides causing GI discomfort, these changes cause variations in the composition of the gut microbiota and create a state of dysbiosis in which the balance between beneficial bacteria and pathogenic bacteria is skewed towards favoring pathogenic species [1]. Furthermore, prolonged and repeated antibiotic use, malnutrition, physical inactivity and stress may exacerbate the effects of autonomic dysreflexia on the gut microbiome [4]. In addition, gut microbiota generates biologically active metabolites that may affect host's phenotypes relevant to cardiovascular disease (CVD) development, ranging from inflammation, obesity, insulin resistance, tissue cholesterol balance and thrombosis risks [5, 6].

Diet may be the key modifiable factor influencing microbiome and metabolic and gastrointestinal health [7]. Although SCI-specific dietary guidelines recommend caloric restriction and a heart-healthy nutrition plan focusing on fruits, vegetables, whole grains, low-fat dairy, poultry, fish and legumes [8, 9], the chronic SCI population does not adhere to dietary recommendations [10–14]. A recent systematic literature review explored nutritional status in chronic SCI [15]. The findings indicated greater energy intake relative to energy needs in those with chronic SCI, and an imbalance in fiber intake and macronutrients (excessive protein and carbohydrate intake) and micronutrients (deficiency of vitamins A, B5, B7, B9, D, E and potassium and calcium) compared to the U.S. Department of Agriculture (USDA) guidelines [15]. In contrast to the general SCI population, competitive athletes are in constant need for optimal nutritional approaches to improve training stimulus and maximize their performance [16]. This means, that athletes often follow a well-balanced diet, designed to ingest a sufficient amount of protein, carbohydrates, fatty acids, vitamins and minerals to cover their macro- and micronutrient requirements. Exercise, in addition, improves GI function [17] and protects against GI disease [18]. Thus, a microbiome of professional athletes seems to have a better profile compared to the microbiome of sedentary individuals [19].

However, in the days before a competition, athletes might adhere to a protein-rich, low fiber diet, which might change bowel motility and gut microbiota [20]. Furthermore, travelling to and change of diet during a competition might further negatively influence the GI system. In a worst-case scenario, significant exercise-constraining GI problems such as cramps and diarrhea may occur during the competition [21]. Probiotics containing various beneficial microbial species, and prebiotics can support and enhance healthy microflora. Both are linked with anti-inflammatory, hypoglycemic, insulinotropic, and antioxidative properties; thus, they may partially compensate pathophysiologic effects of gut dysbiosis and improve short and long-term health in this vulnerable population [22, 23]. Therefore, probiotic supplementation is recommended in order to prevent GI problems during competition or while travelling [24].

Therefore, we hypothesize that probiotic intervention in athletes with SCI may elicit positive changes in GI symptoms, gut microbiome composition and overall health, and potentially lead to improved sport performance. Considering the scarcity of evidence, vulnerability of the target population and peculiarity of dietary and exercise regimes in para-athletes, it is necessary to conduct a pilot study to examine the feasibility of pro- and prebiotic intervention in this population and collect information necessary for sample size calculation of a subsequent trial. In this study, we describe the protocol of a pilot study that assesses the feasibility of a crossover, randomized controlled trial design to assess the effect of probiotics and prebiotics on health of elite Swiss wheelchair para-athletes.

## Methods

### Study design, setting, and sample size

This is a single-center randomized controlled crossover trial adhering to the CONSORT guidelines (Fig. 1) [25] with a total study duration of 12 weeks. A cross-over design offers two advantages over a parallel-group RCT: (1) the influence of confounding covariates are reduced because each participant serves as their own control; and (2) statistical power is higher and required sample size to detect meaningful effects is lower [26]. The study takes place at the Sports Medicine Department within the Swiss Paraplegic Center, the largest SCI-specialized hospital in Switzerland. Each year around 100 wheelchair athletes visit the Sports Medicine Department to perform medical and performance check-ups, thus making a pool of potential study participants. The intervention involves of a 4-week intervention consisting of a daily intake of a multistrain probiotic preparation, or oat bran as prebiotic comparator, followed by a 4-week washout period, and vice versa for four additional weeks (Fig. 2). The method for allocating to intervention (probiotic) or comparator (prebiotic) will be a 1:1 randomization with blocks of two and four executed by a Good Clinical Practice compliant data management system (secuTrial®, interActive Systems, Berlin).

**Fig. 1 Fig1:**
[figure not shown]
The participant flow diagram

**Fig. 2 Fig2:**
[figure not shown]
Summary of study design. Participants are randomized to either probiotic (Bactosan pro-FOS) or prebiotic (oat bran), both taken once a day for 4 weeks (T1), followed by a washout period of 4 weeks (T2) and cross-over to the other intervention for another 4 weeks (T3)

Sample size estimates for the pilot study were done according to published recommendations for minimizing a pilot trial sample size [27]. Here, the use of the stepped rule is recommended in case the standardized effect size to be used in the main trial is unknown. Thus, for a main trial designed with 80% power and two-sided 5% significance, recommended pilot trial sample sizes per treatment arm of 50, 20, 10, and 10 for standardized effect sizes that are extra small (≤ 0.1), small (0.2), medium (0.5), or large (0.8), respectively [27]. We expect to observe a small effect size in the current pilot study and, therefore, we aim to recruit 20 study participants.

### Study participants

Swiss male and female para-athletes above the age of 18 and who are shortlisted for the Paralympic Games 2021 in Tokyo (*n* = 28) or member of a national team (*n* = 15) will be invited to participate. The larger subsequent trial will be recruiting participants among all eligible athletes regularly visiting the Sports Medicine Department and participating in wheelchair sports on a national level (*N* = 100). Exclusion criteria are the presence of chronic inflammatory bowel diseases (ulcerative colitis, Crohn’s disease), taking antibiotics or immunosuppressive drugs, or pregnancy at the beginning of the study. Potential participants will be approached, informed about the study, and screened by phone or in person. After given at least 24 h to consider participation, informed consent will be obtained from all participants. Participants will be redrawn in the following cases: retraction of informed consent, occurrence of a serious adverse advent, a serious sports injury or when any other eligibility criterium is compromised.

### Intervention

#### Probiotic intervention

The probiotic period involves a 4-week supplementation with the commercially available freeze-dried multispecies probiotic preparation Bactosan pro FOS (Mepha, Basel, Switzerland) in addition to usual diet. Following the product guide, the content of one sachet (3 g) will be mixed with 50-100 ml water and taken once daily on an empty stomach before a meal of choice (preferably breakfast). Bactosan pro FOS contains the following bacterial strains: *Bifidobacterium lactis W51, Bifidobacterium lactis W52, Enterococcus faecium W54, Lactobacillus acidophilus W22*, *Lactobacillus paracasei W20*, *Lactobacillus plantarum W21*, *Lactobacillus salivarius W24*, and *Lactococcus lactis W19,* with a total viable cell count of 1 × 10^9^ cfu/g, and therefore 3 × 10^9^ cfu/daily dose. To ensure osmotic stability, survival and biological activity in the GI tract, the following ingredients have been added to the bacterial strains: inulin, fructo-oligosaccharides, amylases, maltodextrin, maize starch and a mineral mix (combination of potassium chloride, magnesium sulphate, and manganese sulphate).

#### Prebiotic comparator

The control period involves a 4-week supplementation with oat bran (Naturaplan, Coop, Switzerland). The participants will consume daily 5 g (one teaspoon) of the oat bran together with a meal of choice in addition to usual diet. The oat bran can be added to the usual breakfast cereal, yoghurt, pancakes, juice, milk, or in an omelet. Based on the findings from a recent systematic review, 40 to 100 g/day of oat bran was shown to increase fecal bacterial mass and short-chain fatty acids in humans [28]. Therefore, we do not expect that the amount of 5 g per day of oat bran cause significant physiological changes in individuals with SCI.

#### Washout period

A 4-week wash-out period was chosen based on the review by Roberfroid [29]. Interventions using inulin-type fructans lead to increases in *Bifidobacteria* which become significant and maximal in less than a week, remain as long as the intake of the prebiotic continues and progressively disappear when the intake stops (within 1–2 weeks) [29]. Although a wash-out period of 2 weeks has been suggested to be sufficient, we extended it to 4 weeks to decrease the possibility of carryover effect.

### Primary outcome measures

#### Feasibility outcomes

Feasibility outcomes were established to explore the methodological, procedural, and clinical uncertainties of the study. These outcomes comprise the recruitment rate, appraisal of the eligibility criteria, completeness of data collection, adherence to the intended supplementation intervention, acceptability of the intervention, participant retention, resources needed to complete the study, safety analyses as well as power analysis of sample size for larger randomized controlled trial (RCT) (the difference between intervention and control/comparator group, and standard deviation). Furthermore, the acceptability of the study among participants will be evaluated post-trial by a combination of open and closed questions regarding the satisfaction with for example the intervention and time burden. All feasibility outcomes are shown in Table 1 alongside the associated progression criteria. The progression criteria are set to facilitate the interpretation of the results and to help us deciding on whether, as well as how, to proceed to a definite trial after the feasibility study. In addition, the results of this pilot study will provide information necessary for the sample size calculation of the future (full-scale) trial.

**Table 1 Tab1:** Overview of feasibility outcomes and progression criteria

Feasibility criteria	Assessment	Progression criteria to a subsequent trial^**a**^
Recruitment and eligibility	Number of eligible athletes	N/A
	Percentage assessed for eligibility; fulfilling inclusion criteria, recruited and included (of total number identified)	> 25% agreed to participate of total eligible population
	Reasons for ineligibility and non-participation	Information to be descriptively summarized. If necessary inclusion/exclusion criteria are to be reconsidered.
Data collection	Percentage of completed assessments/questionnaires	> 75% answering all questions at all assessments
	Numbers of missing items (e.g., laboratory measurements), reasons for missing data collection	< 20% missing information for primary outcomes [30]
Adherence to intervention	A rate of adherence to protocol for both intervention and control interventions	> 80% of participants at baseline
Retention	The number of randomized participants retained/who managed to complete the study protocol Collect the reasons for premature study termination	> 80% of participants at baseline
Feasibility of procedures and experimental setting	Number of: 1. Fasting blood samples collected 2. Correctly taken stool samples by study participants 3. Successfully analysed microbiome composition	> 75% of analytic procedures successfully completed
Acceptability of intervention	Evaluated among participants post-trial: 1. Rating (from 0 to 10) of study procedures (intervention, measurements, time burden, personal value) 2. Willingness to participate again 3. Open feedback	Having an average of at least 5 points for each rating > 50% willing to participate again
Resources needed to complete the study and the intervention	Length of time required for: 1. Study personnel to collect the data the monthly visits 2. Participants to provide data at the monthly visits	< 60 min to complete questionnaires and physical examinations during monthly study visits
Safety analyses	Number of serious adverse events	No serious adverse events related to the study intervention or other procedures.

^a^If one or more criteria are not met revisions should be considered before proceeding to a definite trial

### Secondary outcome measures

#### Sociodemographic characteristics, clinical variables, and gut microbiome composition

Several demographic characteristics will be collected during the baseline visit (T0, Fig. 2) at the study center, including age, sex, SCI (e.g., lesion level and completeness) and highest educational qualification. Body composition will be determined at the baseline visit using a dual X-ray absorptiometry scan (DXA, enCORE v17 Software, Lunar iDXA Serie).

The following data will be collected at each monthly study visit (T0, T1, T2, and T3) at the study center (Sports Medicine Department within the Swiss Paraplegic Center). Secondary health conditions (e.g. urinary and respiratory tract infections) and self-reported medication use. The presence of GI symptoms in the previous 3 weeks will be assessed using the German version of the questionnaire of Eypasch [31], which evaluates the frequency of 36 GI symptoms on a scale from 0 to 4 (0 = never, 4 = all the time). A detailed 3-day food diary based on self-reported intake as well as a 3-day training record for the 3 days prior to the study visit will be completed. The leisure time physical activity questionnaire for individuals with a SCI (LTPA-Q SCI) will be used to assess activity intensity and duration during the last 7 days prior to the study visit [32]. Questionnaires and diaries will be recorded on paper. As a proxy of strength, the average of three maximum handgrip measurements of both hands will be assessed using the Jamar dynamometer (Jamar Hydraulic Hand Dynamometer, Jamar, Bolingbrook, USA). Blood samples will be taken to analyze key markers (e.g., hemoglobin, ferritin, vitamin D) as well as inflammatory markers. A stool sample will be taken at home by the participants within 3 days prior to the study visit using a commercially available kit (OMNIgene®•GUT, DNA Genotek, Ottawa, Canada). The participants bring the stool sample to the study visit and the sample will be used to analyze the microbiome. The Oslo Sports Trauma Research Centre (ORSTC) Questionnaire [33] evaluating illness and injury as well as loss of training days will be filled out weekly by the participants during the entire study and returned to study staff by email or in paper during the study visits. The ORSTC questionnaire plus, when applicable, a reminder to take the supplements, will be emailed to the participants once per week. Despite a daily supplement intake, we have decided to only remind the participants once per week as to not interfere with them too much.

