Finally, the Swiss para-athletes will benefit from an optimal support during the last few months before the Paralympic Games, the major competition happening every 4 years. SCI athletes with neurogenic bowel who will participate in the pilot trial are expected to have a possible benefit, which has been demonstrated for irritable bowel syndrome in the general population [37]. Not only their gut will be prepared to the journey to Japan (e.g., jetlag, hygienic standards, eating habits), but also injury and illness will be monitored weekly. This has been shown to reduce the risk of a major illness or injury due to a fast treatment process based on the close monitoring. Thus, this project will be of major interest concerning research involving the microbiome in SCI, but also athletes and medical staff will benefit in terms of an optimal preparation leading into the Paralympic Games as well as other future competitions.

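### GI symptoms are self-rated by athletes who can tell the two products apart, so the pilot's GI difference may include expectation and should not be used to size the definitive trial

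*Protocol article*

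**What the plan says.** **Products.** Under Probiotic intervention, "the content of one sachet (3 g) will be mixed with 50-100 ml water and taken once daily on an empty stomach". Under Prebiotic comparator, "The participants will consume daily 5 g (one teaspoon) of the oat bran together with a meal of choice". The same section labels the bran period as control ("The control period involves a 4-week supplementation with oat bran") and adds that "we do not expect that the amount of 5 g per day of oat bran cause significant physiological changes". The article mentions no dummy product and no masking.

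**Outcome.** Under Secondary outcome measures, GI symptoms over the previous 3 weeks are collected at T0, T1, T2 and T3 with a paper questionnaire that "evaluates the frequency of 36 GI symptoms on a scale from 0 to 4 (0 = never, 4 = all the time". The athlete supplies every rating.

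**Use of the result.** The Abstract says changes in secondary outcomes will feed a power calculation for the definitive trial, and it lists GI health first among those outcomes. Feasibility outcomes names the difference between intervention and comparator, with its standard deviation, as inputs. Data analyses repeats this for the main secondary outcomes and cites a published crossover formula.

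**Attribution.** Quality assurance and safety provisions asks athletes to keep their usual diet and training, on the ground that any change in health can then be put down only to the supplements.

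**The concern.** The Introduction hypothesises that the probiotic improves GI symptoms, and the measure closest to that hypothesis is the athlete's own report, given in full knowledge of the product. If athletes expect more from one product than from the other, the GI contrast is the product effect plus that difference in expectation, and nothing in the article separates the two.

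Study design justifies the crossover partly because each athlete is his or her own control. That deals with stable differences between athletes and, through randomised order, with period effects. It does not deal with an expectation tied to the product.

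At stake is what the pilot hands on. An inflated GI difference would make the definitive trial look smaller and more achievable than it is. The attribution statement would also lend the GI result more authority than an unmasked self-report can carry. Separately, the acceptability items in Table 1 never ask whether athletes would join a masked comparison, although this pilot could answer that.

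**Working it through.** **1. The plan's own figure.** The stepped rule in Study design, setting, and sample size gives 20 per treatment arm for a small effect (0.2). In a crossover, 20 athletes supply 20 observations per treatment, so the stated 20 is reproduced. The 0.2 is not tied to any named outcome.

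**2. Does the crossover cancel expectation?** Score improvement as positive. Let τ be the product effect, e_P and e_B the expectation effects for probiotic and bran, and π the period effect. Athlete effects drop out of within-athlete differences.

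- Probiotic first: period 1 − period 2 = τ + e_P − e_B − π
- Bran first: period 2 − period 1 = τ + e_P − e_B + π
- Average of the two sequences: τ + (e_P − e_B)

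The period effect goes and the expectation difference stays. A simulation with no product effect and a period effect of 0.15 SD agrees:

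| e_P, e_B (SD) | Estimated difference |
|---|---|
| 0.2, 0 | 0.201 |
| 0.3, 0.1 | 0.195 |
| 0.2, 0.2 | −0.001 |

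Only unequal expectation biases the contrast.

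**3. Illustrative effect on the definitive sample size.** From the article: two-sided 5%, 80% power, effect 0.2. Assumed: the 0.2 applies to the GI score in units of the SD of paired differences; the expectation difference b is 0.1, 0.2 or 0.3 in the same units; the definitive trial is itself free of this bias.

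N = (1.960 + 0.842)² / (0.2 + b)² = 7.849 / (0.2 + b)²; true power = Φ(0.2√N − 1.96).

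| b (assumed) | Apparent effect | Implied N (nearest integer) | Power for the true 0.2 |
|---|---|---|---|
| 0 | 0.2 | 196 | 80% |
| 0.1 | 0.3 | 87 | 46% |
| 0.2 | 0.4 | 49 | 29% |
| 0.3 | 0.5 | 31 | 20% |

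For comparison, Study participants puts the definitive pool at 100 athletes.

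**4. Sensitivity to the unit.** If 0.2 and b are instead in between-athlete SDs, N = 7.849 × 2(1 − ρ)/(0.2 + b)², rounded up to an even number, where ρ is the within-athlete correlation (not given in the article).

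| ρ (assumed) | N, b = 0 | N, b = 0.2 |
|---|---|---|
| 0.3 | 276 | 70 |
| 0.5 | 198 | 50 |
| 0.7 | 118 | 30 |
| 0.8 | 80 | 20 |

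The absolute numbers move a good deal. The proportional fall, and the true power of 29% at b = 0.2, do not.

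**5. If the definitive trial were also unmasked.** With no true effect, a trial sized for 0.2 SD would be significant about 29% of the time at b = 0.1 and about 80% at b = 0.2.

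**6. Scale.** The score runs from 0 to 36 × 4 = 144. With an assumed SD of 10 to 25 points, 0.2 SD is 2 to 5 points. The pilot's own 95% half-width with 20 athletes is 2.093/√20 = 0.47 SD of the paired differences, wider than any shift assumed above.

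**The case against.** **The GI score is not named as the basis for sizing.** The primary outcome is feasibility, analysed descriptively, and no GI result is a progression criterion. The example outcomes in Data analyses are body composition, glucose, C-reactive protein and cholesterol, which are much less open to expectation. This stands as a limit on how likely the harm is. It does not remove the harm, because the Abstract and Data analyses refer to secondary outcomes generally and GI health is among them.

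**Unequal expectation is not shown.** A reader might take "SCI athletes with neurogenic bowel who will participate in the pilot trial are expected to have a possible benefit" as a promise attached to the probiotic. The sentence concerns taking part, and every athlete is due to take both products. The Introduction and Discussion also speak well of prebiotics. The control label is wording in a journal article, and what athletes are told is not shown. All of this stands: unequal expectation is plausible, not established.

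**The size is assumed.** A reader might infer that expectation could account for the whole effect the plan expects. The documents give no expectation effect, GI score SD or correlation, and their 0.2 belongs to no particular outcome, so that inference is arithmetic on assumptions.

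**Sampling error is larger.** A half-width of 0.47 SD means chance alone could move the implied N by more than the assumed bias. That is true, and it is a second reason not to size on the observed mean difference.

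**Conclusion.** The point holds in limited form. The products are distinguishable and the GI rating is the athlete's own, so any difference in expectation between products remains in the within-athlete GI difference. The plan to carry between-product differences forward therefore needs a restriction for this outcome, and the attribution statement does not hold for an unmasked self-report.

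The direction and size of the bias are unknown. The fall in N from about 196 to between 87 and 31, with true power of 46% to 20%, rests on an assumed true effect of 0.2 SD of the paired differences, assumed shifts of 0.1 to 0.3 SD, and a definitive trial free of the same bias.

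It would be wrong to conclude that the pilot is invalid. Recruitment, retention, adherence and the other progression criteria do not depend on this contrast. This is a cheap improvement to what the pilot can pass on.

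**What to change.** 1. Report the GI difference as an unmasked comparison, and qualify the attribution statement in Quality assurance and safety provisions for self-reported outcomes.
2. Do not size the definitive trial on the observed GI mean difference. Use the pilot's within-athlete SD with a minimum important difference set in advance. An expectation shift common to all athletes leaves that SD unchanged.
3. Add one closed post-trial item to the acceptability row of Table 1: would the athlete join a trial without being told which product is being taken?
4. Optionally, collect expectation ratings for each product at T0 and report them descriptively. They should not be used for covariate adjustment with about 20 athletes: the estimate would be imprecise and, if most athletes favour the same product, would rest on extrapolation.

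The cost is one closed item, plus the T0 ratings if used, and a more cautious statement of the GI result. Product, dose, schedule and visits are untouched.
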